### Intervention

#### Tailored BPL Group

During surgery, the surgeon will measure the TSBL. The BPL length will be determined as 40% of the TSBL. The rationale for this approach is to ensure a common channel length of at least 250–300 cm.

#### Standard BPL Group

During surgery, the surgeon will measure the TSBL. The BPL length will be measured and set to a fixed length of 180 cm.

#### Surgical Technique

All surgeries will be performed laparoscopic or robotic approach by MBS surgeons at the participating centers, adhering to standardized OAGB techniques. The dissection to create the gastric pouch begins below the level of the crow’s foot, and the pouch is created using a 40 Fr bougie for calibration, with the aim of constructing a pouch of at least 15 cm in length. The ligament of Treitz is identified and the TSBL is measured by a visual estimation. The anastomosis is performed in a side-to-side manner using a linear staple (30–40 mm) and the anastomotic opening is closed using a barbed suture. A routine blue dye leak test is performed. Mesenteric defects are not closed routinely.

### Postoperative Care

Patients are admitted postoperatively to the surgical ward and an Enhanced Recovery After Surgery (ERAS) protocol [12] is applied to all patients including early mobilization, fluid drinking at the evening of surgery, abstention of intravenous fluids and catheters. Patients are planned to be discharged on postoperative day 1. Criteria for patient discharge are shown on Table 2. All patients receive high-dose proton pump inhibitors (20 mg twice per day) for 3 months and continued venous thromboembolism prophylaxis with subcutaneous injection of enoxaparin 40 mg for three weeks. In addition, patients will be prescribed a standardized multivitamin supplement regimen as recommended by a clinical nutritionist, in accordance with established guidelines for postoperative care following MBS.

**Table 2 Tab2:** Discharge criteria for patients after OAGB

• Patients ambulate freely with no assistance
• Postoperative pain controlled with non-opioid analgesia
• Vital signs within normal limits (pulse rate < 100/min; temperature < 37.5 °C; O_2_ saturation > 92%, mean blood pressure — 70–100 mmHg
• Ability to tolerate a minimum of 1500 mL of oral fluids within 24 h prior to discharge
• Absence of clinical indicators of postoperative complications
• Comprehensive understanding of post-discharge care and scheduled follow-up

### Data Collection

Data will be collected prospectively at baseline, intra-operatively, and during follow-up visits.

The following data points will be collected:Demographics: Age, genderPre-operative: Weight, height, Body Mass Index (BMI), obesity-related conditions, previous abdominal surgeries, ASA score, Charlson comorbidity index (CCI), blood test results (hemoglobin, platelets, creatinine, albumin, vitamin D, B12, folic acid, iron, ferritin, transferrin, glucose, HbA1c, lipid profile, liver, thyroid and parathyroid function tests)Intra-operative: Date of surgery, duration of surgery, total small bowel length (cm), BPL length (cm), intra-operative complications.Post-operative: Post-operative complications (bleeding, leak, wound infection, VTE, surgical site infection), grading of complications according to Clavien-Dindo grading of complications [13], length of hospital stay, 90-day readmissions, 90-day reoperations.Follow-up (6 months, 1 year, 3 years): Weight, height, BMI, obesity-related conditions during follow-up, blood test results (as above), > 90-day complications, reoperations, quality of life measures will be measured according to the BAROS questionnaire [14]. Bowel habits and stool characteristics will be assessed according to the Fecal Score [15].

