### Follow-Up

Participants will be followed up at 2 weeks, 3 months, 6 months, 12 months, and annually thereafter. At each visit, weight, obesity-related diseases, and any complications will be assessed. Blood tests will be performed at 3–6 month intervals to monitor nutritional status.

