### Outcome Measures

#### Primary Outcome

The primary outcome is the difference in percentage of total weight loss (%TWL) between the two groups at 1 and 3 years postoperatively.

%TWL will be calculated as: (Pre-operative weight – Follow-up weight)/Pre-operative weight) × 100.

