### Follow-Up Rate

Based on our previous experience in similar studies conducted at our center [19, 20], we anticipate a loss to follow-up rate of 10–20% after 3 years. Measures will be taken to minimize attrition, including scheduled follow-up reminders and coordination with clinical teams to ensure patient engagement throughout the study period.

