### Data Analysis

Statistical analysis will be performed using IBM SPSS Statistics software version 29. Continuous variables will be presented as means ± standard deviations, and categorical variables will be presented as frequencies and percentages. Baseline characteristics of the two groups will be compared using independent *t*-tests for continuous variables and chi-square tests for categorical variables.

The primary outcome (%TWL) will be compared between the two groups using an independent *t*-test. If data are not normally distributed, a Mann–Whitney *U* test will be used. Changes in obesity-related diseases and quality of life scores will be analyzed using paired *t*-tests or Wilcoxon signed-rank tests (as appropriate) to compare pre- and post-operative values within each group. Differences between groups will be assessed using independent *t*-tests or Mann–Whitney *U* tests. The incidence of complications will be compared between the two groups using chi-square tests or Fisher’s exact tests.

Multivariable regression analysis will be used to adjust for potential confounders (e.g., baseline BMI, comorbidities) in the analysis of the primary outcome. A *p*-value of < 0.05 will be considered statistically significant.

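### The follow-up schedule has weight assessed at 24 months, but the itemised trial-data list omits that visit; the two sections should be reconciled (minor)

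*Protocol article*

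**What the plan says.** Two sections of the protocol article describe when follow-up information is gathered.

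- **Follow-Up** sets the visits: "Participants will be followed up at 2 weeks, 3 months, 6 months, 12 months, and annually thereafter". It then fixes their content: "At each visit, weight, obesity-related diseases, and any complications will be assessed". A 24-month weight follows from these two sentences.
- **Data Collection** opens with a general statement, "Data will be collected prospectively at baseline, intra-operatively, and during follow-up visits", and then itemises the data points. The follow-up item reads "Follow-up (6 months, 1 year, 3 years): Weight, height, BMI, obesity-related conditions during follow-up". It has no 24-month entry, and none for 2 weeks or 3 months.

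Three other sections bear on the point. Primary Outcome states: "The primary outcome is the difference in percentage of total weight loss (%TWL) between the two groups at 1 and 3 years postoperatively". Follow-Up Rate says "we anticipate a loss to follow-up rate of 10–20% after 3 years". Data Analysis says "The primary outcome (%TWL) will be compared between the two groups using an independent *t*-test", with a Mann–Whitney test if the data are not normal and a multivariable regression for adjustment. Sample Size rests on the 3-year comparison.

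**The concern.** A centre that builds its data form from the itemised list would have no 24-month field. A centre that works from the Follow-Up section might record one. With three or four centres, capture could differ between them.

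The 24-month weight is the scheduled measurement closest before the 3-year outcome on which the trial is sized. If a patient attends at 24 months and misses 36, it is the best available evidence on what the 3-year value would have been, including any regain after year 1. Without it, the last listed trial weight for that patient is the 1-year value. An analysis plan can choose how to treat missing 3-year values, but it cannot use a weight that was never entered. Weights retrieved later from clinic records may be incomplete or uneven across centres.

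**Working it through.** **1. The two sections side by side**

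| Visit | Follow-Up section: weight assessed | Data Collection list: weight named |
|---|---|---|
| 2 weeks, 3 months | yes | no |
| 6 months, 12 months | yes | yes |
| 24 months | yes | no |
| 36 months | yes | yes |

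The general opening sentence of Data Collection excludes no visit, but the list that follows is the specific text and it names times. The mismatch is real.

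**2. The plan's own figure**

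Inputs from Sample Size: difference 5 points, SD 12, power 0.80, alpha 0.05 (taken as two-sided). n per arm = 2 × 12² × (1.960 + 0.842)² / 5² = 90.4, so 91, against the stated 90. Enrolment: 180 × 1.10 = 198, as stated (180 / 0.90 would give 200). The figure reproduces closely, and the 24-month weight does not enter it.

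**3. Who could benefit**

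Losses by year 3 are 198 × 0.10 = 19.8 to 198 × 0.20 = 39.6 patients. Only those lost between the 24- and 36-month visits have a 24-month weight to add. If half of the losses fall there (an assumption), that is 9.9 to 19.8, about 10 to 20 patients over both arms.

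**4. The planned t-test**

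It uses only patients with a 3-year weight. With 99 enrolled per arm, 10% loss leaves 89.1 and 20% leaves 79.2. Power = Φ(5 / (12 × √(2/n)) − 1.96) gives 79.4% and 74.6%, with or without a 24-month weight.

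**5. An analysis that uses earlier weights**

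Assumptions not in the document: data missing at random, losses split evenly around month 24, all lost patients have a 12-month weight, and the correlations of %TWL given below. Write r13, r23 and r12 for the 12/36-, 24/36- and 12/24-month correlations. Let A = r13² and B = (r13² + r23² − 2·r13·r23·r12) / (1 − r12²). Let f2 and f3 be the fractions seen at 24 and 36 months. Relative to full follow-up, the variance of the 36-month mean is

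- 12-month weight only: A + (1 − A)/f3
- 12- and 24-month weights: A + (B − A)/f2 + (1 − B)/f3

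The effective n per arm is 99 divided by this factor.

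Example: r13 = 0.6, r23 = r12 = 0.8, 20% loss, so f2 = 0.9 and f3 = 0.8. A = 0.36. B = (0.36 + 0.64 − 0.768)/0.36 = 0.644. The factors are 0.36 + 0.64/0.8 = 1.160, and 0.36 + 0.284/0.9 + 0.356/0.8 = 1.120. Effective n is 85.3 and 88.4; power is 77.7% and 79.1%.

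| r13 / r23 / r12 | 20% loss: effective n, 12-month only → with 24-month | 20% loss: power | Gain at 20% loss | Gain at 10% loss |
|---|---|---|---|---|
| 0.5 / 0.7 / 0.7 | 83.4 → 85.8 | 76.7% → 77.9% | 1.2 points | 0.5 points |
| 0.6 / 0.8 / 0.8 | 85.3 → 88.4 | 77.7% → 79.1% | 1.4 points | 0.6 points |
| 0.7 / 0.85 / 0.85 | 87.8 → 90.4 | 78.8% → 80.0% | 1.2 points | 0.5 points |
| 0.6 / 0.9 / 0.7 | 85.3 → 90.2 | 77.7% → 79.9% | 2.2 points | just under 1 point |
| 0.8 / 0.95 / 0.85 | 90.8 → 94.0 | 80.2% → 81.5% | 1.3 points | 0.6 points |

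At 20% loss, the step from completers only (74.6%) to use of the 12-month weight (76.7–80.2%) is worth 2.1 to 5.6 points. That weight is already on the list.

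**The case against.** The strongest reply is that nothing in the article says the 24-month weight goes unrecorded. Data Collection speaks of follow-up visits in general, and Follow-Up has weight assessed at each. The bracketed times head a bundle that includes the BAROS questionnaire and the Fecal Score, which their own sections set at 6, 12 and 36 months. The bracket may therefore mark the full assessments, with Follow-Up governing weight. This stands in part: a reader might infer that the 24-month weight is discarded, but that is only the literal reading of one list and not a stated rule. What remains is that two sections give different times and neither defers to the other.

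A second reply is that data-form fields and missing-data methods belong in a full protocol or analysis plan that is not shown. That is right for the absence of such detail, and no absence is claimed here. The article prints both schedules, and they differ.

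A third reply is that the planned test ignores intermediate weights, so capturing this one changes nothing by itself. This stands. The benefit needs a change or addition to the analysis as well. Gathering fewer time points for a trial than for clinical follow-up is also an ordinary choice, if it is made openly.

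**Conclusion.** The inconsistency holds and is minor. Weight and obesity-related diseases are assessed at 24 months under one section and are not listed as trial data at that time under the other.

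Two stronger conclusions are tempting and are not supported. The first is that everyone lost before year 3 lacks weight information after month 12 because of the list. Patients lost before the 24-month visit have none under either section; only those seen at 24 but not at 36 months are affected. The second is that a 24-month weight would lift power from about 75% to 80% or more. Most of that rise comes from using the 12-month weight.

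The 24-month weight itself is worth about 1 to 2 power points at 20% loss and under 1 at 10%. These figures rest on the assumed correlations, an even split of losses around month 24, and data missing at random. The protection against attrition bias is plausible, since the last observation would be a year closer to the endpoint, but the document gives no basis for putting a number on it.

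**What to change.** Add the 24-month weight and obesity-related conditions to the follow-up item in Data Collection, so that it agrees with Follow-Up on that visit. State also whether the 2-week and 3-month weights are trial data; they matter little for the 3-year outcome, but the same mismatch applies.

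Then use the 12- and 24-month %TWL in a repeated-measures or multiple-imputation analysis of 3-year %TWL, in place of the t-test in Data Analysis or alongside it, and say in advance which result is primary.

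The cost is one more set of fields for a visit already scheduled and some added analysis work. No extra visit, procedure or patient is needed, and the enrolment target does not change. It is best done before patients reach month 24, while the values can still be entered prospectively and in the same way at every centre.

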### Follow-Up

Participants will be followed up at 2 weeks, 3 months, 6 months, 12 months, and annually thereafter. At each visit, weight, obesity-related diseases, and any complications will be assessed. Blood tests will be performed at 3–6 month intervals to monitor nutritional status.

### Ethical Considerations

This study was approved by the Institutional Review Board (IRB) of Tel Aviv Sourasky Medical Center (Approval No. TLV-24-0586) on January 23, 2025. All data will be collected and stored in compliance with data privacy regulations. Participant data will be de-identified and stored securely on password-protected servers at the participating centers.

### Outcome Measures

#### Primary Outcome

The primary outcome is the difference in percentage of total weight loss (%TWL) between the two groups at 1 and 3 years postoperatively.

%TWL will be calculated as: (Pre-operative weight – Follow-up weight)/Pre-operative weight) × 100.

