**Methods:**

This multicenter, prospective, randomized trial will enroll at least 200 participants undergoing OAGB across three centers. Participants, aged 18 and older, will be randomized into two groups: one group will undergo a tailored BPL length based on TSBL (40%), while the control group will receive a standard BPL length of 180 cm. The primary endpoint is comparison of total weight loss after 1 and 3 years. Secondary endpoints include postoperative complications, quality of life, and improvements in obesity-related diseases.

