The outcomes of patients after OAGB with a tailored BPL length are unclear. It is possible that these patients could have higher weight loss and metabolic outcomes. The purpose of this study is to evaluate if personalized tailoring of the BPL length to TSBL is effective and safe. Our primary outcome will investigate if tailored BPL is more effective in terms of percentage of total weight loss at 3 years compared to patients undergoing OAGB with a standard BPL length. We will also record perioperative and malnutrition-related outcomes in order to investigate the safety profile of the tailored BPL arm in comparison to the standard arm. We hypothesize that tailoring the BPL length to a percentage of the TSBL in patients undergoing OAGB will result in greater total weight loss after 1 and 3 years and result in comparable safety outcomes, including perioperative and malnutrition-related complications, compared to a fixed standard BPL length. We hereby present the protocol of the *T*ailored *B*iliopancreatic *L*imb *LE*ngth to 40% of TSBL study (TABLE-40 study).

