### Statistical Analysis

#### Sample Size

Based on the previous literature of study cohorts which are similar to our expected study population [21–23], our hypothesis is that at 3 years the tailored group will have a 5% higher %TWL in comparison to the fixed group (40% vs. 35%). In order to detect a difference in %TWL at 3 years with a power of 0.8 and an alpha significance of < 0.05 and standard deviations of 12, 90 patients are needed in each arm for a total of 180 patients. Assuming a drop-out rate of 10%, enrollment of 198 patients is needed for sufficient power for the trial.

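### The protocol article contradicts itself on the primary time point: 1 and 3 years in some places, 3 years only in the primary-outcome sentence of the Introduction and in the sample size

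*Protocol article*

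**What the plan says.** Five statements in the protocol article bear on the primary time point.

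- Primary Outcome section: "The primary outcome is the difference in percentage of total weight loss (%TWL) between the two groups at 1 and 3 years postoperatively".
- Abstract, Methods: "The primary endpoint is comparison of total weight loss after 1 and 3 years".
- Introduction, last paragraph, primary-outcome sentence: "Our primary outcome will investigate if tailored BPL is more effective in terms of percentage of total weight loss at 3 years".
- Introduction, same paragraph, hypothesis: the tailored limb "will result in greater total weight loss after 1 and 3 years".
- Sample Size section: "our hypothesis is that at 3 years the tailored group will have a 5% higher %TWL", and, on the numbers, "with a power of 0.8 and an alpha significance of < 0.05 and standard deviations of 12, 90 patients are needed in each arm".

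The Data Analysis section compares %TWL between the arms with an independent t-test (Mann–Whitney if not normal) and does not name a time point. It closes with one general significance threshold of p < 0.05. The article gives no ranking of the two years, no division of alpha, and no rule on whether one or both must be significant.

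**The concern.** The two sets of statements cannot both define the primary outcome. One set makes %TWL at two time points primary, and the other makes it primary at 3 years alone. Nothing elsewhere in the article reconciles them.

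This matters because the 1-year data arrive two years before the 3-year data. Under the Primary Outcome section, a significant 1-year difference could be reported as meeting the primary outcome before the time point used for the sample size has been observed. If the difference then faded by 3 years, the published text would support a positive conclusion under one section and a negative one under another. Patients and surgeons know the allocation, which is a further reason to have the decisive comparison fixed beyond dispute in advance.

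**Working it through.** **Inputs from the Sample Size section.** Difference 5 percentage points (40% vs. 35%) at 3 years, SD 12, alpha 0.05, power 0.80, 90 per arm. Sidedness is not stated. The correlation between the 1-year and 3-year test statistics is not given, so it is assumed over a range.

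**Step 1: reproduce the plan's figure.** For two means, n per arm = 2 (z₁₋α/₂ + z₁₋β)² SD² / Δ².

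- Two-sided 5%: 2 × (1.960 + 0.842)² × 144 / 25 = 90.4, so 91 after rounding up, against 90 stated.
- One-sided 5% would give 72, so the plan used a two-sided test.
- Power at 90 per arm: 5 / (12 × √(2/90)) = 2.795, and Φ(2.795 − 1.960) = 79.8%. The t-distribution version gives 79.4%.

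The stated sample size is therefore that of one two-sided 5% test at 3 years. No alpha or power has been set aside for a second primary test.

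**Step 2: if success at either year counted.** With each test at two-sided 0.05, the type I error is 1 − P(|Z₁| < 1.96 and |Z₂| < 1.96), with Z₁ and Z₂ bivariate normal with correlation ρ. At ρ = 0 this is 1 − 0.95² = 9.75%, which is the maximum.

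| Assumed ρ | Type I error |
|---|---|
| 0 | 9.75% |
| 0.3 | 9.51% |
| 0.5 | 9.07% |
| 0.6 | 8.75% |
| 0.7 | 8.35% |
| 0.8 | 7.81% |
| 0.9 | 7.04% |
| 0.95 | 6.46% |

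**Step 3: if both years had to be significant.** The type I error does not exceed 5%. Joint power cannot exceed the power at 3 years, and it is lower unless success at 1 year is almost certain. If 1-year power were also 80%, joint power would be 0.80² = 64% at ρ = 0, and 68.7%, 69.9%, 71.3% and 72.9% at ρ = 0.5, 0.6, 0.7 and 0.8. The 80% at 1 year is an assumption, because the article gives no 1-year difference or SD. Higher 1-year power would bring joint power closer to the 3-year figure, and lower 1-year power would reduce it further.

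**Step 4: if 3 years alone is primary.** Alpha stays at 5% and power is 79.8% at 90 per arm. Of the three readings, this is the one that matches the stated error rate and, within rounding, the stated power.

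**Step 5: if alpha were split equally (0.025 each).** 2 × (2.241 + 0.842)² × 144 / 25 = 109.5, so 110 per arm, 220 in total, and 220 / 0.90 = 244.4, so 245 enrolled at 10% dropout. With 90 per arm, power for a 5-point difference at one time point would be 71%.

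**The case against.** The strongest reply is that this is a condensed article. A testing order, an alpha split or a success rule may stand in a full protocol or SAP that is not shown, and its absence here is no fault. That stands, and the missing rule is not the point being made. The reply does not cover conflicting statements: a rule elsewhere would not make the article's own definitions of the primary outcome agree.

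A second reply is that the text can be read benignly, with 3 years as the powered confirmatory comparison and 1 year as an earlier look at the same measure. That reading fits the Introduction's primary-outcome sentence and the sample size. It does not fit the Primary Outcome section or the Abstract, which put the two years on the same footing.

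A reader might go further and infer that the trial tests each year at p < 0.05 and so has a false-positive rate of about 8–9%. The documents do not support that as a statement of fact, for three reasons.

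- It requires that either year suffices, which is nowhere stated. If both are required, there is no inflation.
- It requires a correlation of about 0.5 to 0.77, which is nowhere given.
- The Data Analysis section states one general threshold. Applying it separately to each year is an inference.

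Nor can it be said that the Introduction as a whole names only 3 years, since its hypothesis names both.

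**Conclusion.** The contradiction is firm and rests on the printed text alone. The Primary Outcome section, the Abstract and the hypothesis name 1 and 3 years; the Introduction's primary-outcome sentence and the sample size name 3 years only. It is also firm that 90 per arm provides for one two-sided 5% test at 3 years, with about 79–80% power, and for nothing more.

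The size of the consequence is conditional. An either-year rule would raise the type I error above 5% at every correlation below 1. A both-years rule would leave the error rate intact and cost power, by an amount that depends on a 1-year power that the document does not supply. The article does not say which rule applies, so neither figure is a property of the trial as written. The point should be settled before 1-year results are compared by arm.

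**What to change.** Name %TWL at 3 years as the single primary outcome in the Abstract, the Introduction (including the hypothesis) and the Primary Outcome section, matching the Sample Size section. Make %TWL at 1 year a key secondary outcome, tested confirmatorily only if the 3-year comparison is significant. Label any earlier 1-year report as secondary.

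The cost is a wording amendment, with notification of the registry and the IRB if needed. No confirmatory 1-year claim can be made before the 3-year result is known. No extra patients, visits or data are required.

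If the sponsor wants both years to be primary, the success rule must be stated and the sample size redone. An equal alpha split needs 110 per arm by the plan's own inputs. Requiring both needs a stated 1-year difference and SD from which joint power can be computed.
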